### Data collection plan

Data will be record and assessed as per the subjective and objective criteria on 0
^th^, 15
^th^, 30
^th^ & 45
^th^ of study (see
Table 1).

**Table 1. T1:** The plan for collection of data.

Group	Sample size	Intervention	Dose and frequency	Anupan	Duration	Follow Up
A	30	*Trayodashang Guggul*	500 mg Twice a day after meal	Warm Water	30 days	0 ^th^,15 ^th^, 30 ^th^ day during treatment 45 ^th^ day after treatment
B	30	*RasonaPinda*	500 mg twice a day after meal	Warm water	30 days	
	** *Katibasti* (oil pooling therapy) with *Dashmool oil* in both groups**				Initial 7 days	

Ayurveda samhitas

Modern texts

Online search – Google scholar, etc.

60 patients

*TrayodashangGuggul*

RasonaPinda

Case record form

Patients information form

Written and informed consent form

Measuring scale

Sphyghmomanometer

Weighing machine

Data obtained from the follow up chart and other observations will be used and the results will be drawn on the basis of various charts, graphs, and tables. To determine the relevance of the findings, improvement in patient condition as per assessment criteria, after treatment will be noted as significant.

**
*Drug collection/authentication*
**

The department of Dravyaguna and Rasashastra of Mahatma Gandhi Ayurved college hospital and Research Center, Salod, Wardha will validate and identify the raw material before it is used to make the medicine. It will be obtained from a reputable source.

**
*Statistical methods*
**

Descriptive statistics will summarize baseline characteristics. Baseline comparisons between groups will be conducted using independent t-tests for continuous variables and Chi-square tests for categorical variables. Primary outcome analysis will involve paired t-tests (or Wilcoxon signed-rank tests) within each group to evaluate changes from baseline, and independent t-tests (or Mann-Whitney U tests) to compare changes between groups. Secondary outcomes will be analyzed using repeated measures ANOVA or mixed-effects models for longitudinal data, and Chi-square tests for categorical outcomes. Regression analyses will adjust for potential confounders.

**
*Study status*
**

IEC Clearance and CTRI registration has been done. Recruitment of patient has started as per the inclusion and exclusion criteria.

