### Recruitment

As per sample size calculation, total patients will be recruited. Data collected will be analyzed by using appropriate statistical methods. The patients of
*Grudhrasi* will be selected from the Kayachikitsa Out-patient department and In-patient department of Mahatma Gandhi Ayurved College, Hospital & Research Centre, Salod (H), and from specialized peripheral camps.

**
*Enrolment and interventions time schedule*
**

The intervention period will be from 0 to 30 days and follow up on the 0
^th^, 15
^th^, 30
^th^ and 45
^th^ day.

**
*Sample size*
**

Formula using Mean difference:

$$n1=n2=2\frac{{\left(Z_{\alpha }+Z_{\beta }\right)}^{2}\sigma^{2}}{{\left(\delta \right)}^{2}}$$

$Z_{\alpha }=1.96$

α=Type I error at 5% at both sides two tailed

$Z_{\beta }=0.84=\text{Power at 80\%}$

Primary Variable = Radiation of Pain

(Mean) value of Radiation of Pain for Trayodashangguggul treatment group (Before) = 2.27 (As per reference article).
^
19
^

(Mean) value of Radiation of Pain for Trayodashangguggul treatment group (After) = 0.93.

Mean Difference for the effect in Trayodashangguggul after and before 2.27 – 0.93 = 1.34.

Standard Deviation = 0.62

Considering 20% clinically relevant margin for RasonaPinda

$\left(\delta \right)$
 = (1.34 *35) /100 = 0.469.

Sample size N =

$n1=n2=2\frac{{\left(1.96+0.84\right)}^{2}{\left(0.62\right)}^{2}}{{\left(0.469\;\right)}^{2}}=28\;\text{per group}$

Considering 10% drop out = 2

Total sample size required = 28 + 2 = 30 per group.

A total of 60 patients will be recruited for the study.

**Allocation sequence generation** – Computer-Generated Randomization.

**Concealment of allocation** – assessor blinding.

**Allocation implementation** – the first author will generate an allocation sequence, enrol participants, and assign participants to intervention.

**Blinding –** randomized single blind standard controlled superiority clinical trial.

The outcome assessor will be blinded.

Unblinding will not be permissible to outcome assessor.

Participant will be revealed about allocation of intervention at the time of enrolment.

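### The primary between-group test compares change scores without baseline adjustment: valid, but a single baseline-adjusted comparison would generally be more precise at almost no cost

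*Protocol article*

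**What the plan says.** The Statistical methods text, under Data collection plan, gives the primary analysis two parts: paired tests within each arm, and "independent t-tests (or Mann-Whitney U tests) to compare changes between groups". Repeated-measures ANOVA and mixed-effects models are named for secondary outcomes only.

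The same paragraph adds: "Baseline comparisons between groups will be conducted using independent t-tests for continuous variables and Chi-square tests for categorical variables". It closes with "Regression analyses will adjust for potential confounders", which names neither an outcome nor any covariate.

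The sample size text, under Recruitment, gives "Primary Variable = Radiation of Pain" and builds its target difference from a before-after change in the reference treatment. It gives an SD of 0.62 without saying whether this is the SD of the change or of a single score. No correlation between baseline and follow-up appears anywhere. Study setting says that all parameters are recorded at days 0, 15, 30 and 45, and describes simple randomisation of 60 patients.

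**The concern.** A change-score comparison subtracts the whole baseline value from each patient's follow-up value, in effect fixing the baseline coefficient at 1. Analysis of covariance (ANCOVA) estimates that coefficient from the data. When the true slope is below 1, subtraction over-corrects: the arm that happens to start worse appears to improve more. Under simple randomisation with about 30 per arm, such imbalance is to be expected by chance.

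The baseline significance tests give no protection. In a randomised trial they test a hypothesis known to be true, and an imbalance large enough to move the estimate will usually be non-significant.

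What is at stake is precision. The day-0 score is due to be recorded anyway, and the trial is sized for only 80% power.

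**Working it through.** **Inputs from the sample size text.** "α=Type I error at 5% at both sides two tailed", so z = 1.96; power 80%, so z = 0.84; "Mean Difference for the effect in Trayodashangguggul after and before 2.27 – 0.93 = 1.34"; target difference "1.34 *35) /100 = 0.469"; SD 0.62; 28 evaluable per group.

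**The plan's own figure.** n = 2 × (1.96 + 0.84)² × 0.62² / 0.469² = 2 × 7.84 × 0.3844 / 0.21996 = 27.4, rounded up to 28 per group. It reproduces. Power of the unadjusted two-sample test at 28 per group is 80.8% by the normal approximation and 79.4% by the noncentral t distribution. The powers below use noncentral t, with one degree of freedom charged for the covariate under ANCOVA.

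**Variance comparison.** Let s be the SD at baseline, ks the SD at follow-up and r their correlation.

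- Change score: s²(1 + k² − 2rk)
- ANCOVA: s²k²(1 − r²)
- Difference: s²(1 − rk)², which is never negative

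So, apart from the small cost of estimating one coefficient, ANCOVA is never less precise, and the advantage disappears as rk approaches 1. With equal variances (k = 1), the ratio of ANCOVA to change-score variance is (1 + r)/2.

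**Reading A: 0.62 is the SD of change, k = 1.** The effective SD becomes 0.62 × √((1 + r)/2).

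| Assumed r | Variance reduction | Effective SD | Change-score power | ANCOVA power |
|---|---|---|---|---|
| 0.3 | 35% | 0.500 | 79.4% | 93.1% |
| 0.5 | 25% | 0.537 | 79.4% | 89.4% |
| 0.7 | 15% | 0.572 | 79.4% | 85.4% |

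The gain is about 6 to 14 points.

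**Reading B: 0.62 is the SD of a single score, k = 1.** The SD of change is 0.62 × √(2(1 − r)) and the ANCOVA SD is 0.62 × √(1 − r²).

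| Assumed r | SD of change | ANCOVA SD | Change-score power | ANCOVA power |
|---|---|---|---|---|
| 0.3 | 0.734 | 0.591 | 65.2% | 83.0% |
| 0.5 | 0.620 | 0.537 | 79.4% | 89.4% |
| 0.7 | 0.480 | 0.443 | 94.8% | 97.3% |

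The gain is about 2 to 18 points.

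**Unequal variances, 0.62 as SD of change.** If the follow-up SD is 1.5 times the baseline SD (assumed), the variance ratios are 0.871, 0.964 and 0.998 for r = 0.3, 0.5 and 0.7. ANCOVA power is then 84.5%, 80.8% and 79.4%, so the gain runs from 5 points to nil. If the follow-up SD is 0.7 times the baseline SD (assumed), the gain is about 18 to 20 points.

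**Chance imbalance, reading A, r = 0.5.** The single-score SD is 0.62 / √(2 × 0.5) = 0.62. The standard error of the baseline difference is 0.62 × √(2/28) = 0.166. An imbalance of one standard error shifts the change-score estimate by (1 − 0.5) × 0.166 = 0.083, which is 18% of 0.469. The same calculation gives 21% at r = 0.3 and 14% at r = 0.7. One standard error is far from significance in the planned baseline test.

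**The case against.** The strongest defence is that nothing here is wrong. A change-score comparison is unbiased over randomisation, it matches a sample size built on a before-after difference, and at the stated inputs it delivers about 80% power. That stands: a reader might infer that the planned test is invalid, and it is not.

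Four other stronger readings are tempting and are not supported.

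- **A gain of about 10 power points.** This is right near r = 0.5 with equal variances. The document gives no correlation, does not say what 0.62 measures, and does not give separate baseline and follow-up SDs. The outcome also looks like a short graded scale with a mean falling from 2.27 to 0.93, so equal variances are doubtful and linear-model power is approximate.
- **Covariates will be picked from the baseline tests.** The text does not say so. A covariate list is detail that an article may leave to the full plan.
- **Several competing primary p-values.** The t-test or Mann-Whitney comparison is the one labelled primary, and the rule for choosing between them may also sit in the full plan. The regression sentence is not tied to the primary outcome.
- **Adjustment rescues a trial short of power for a 20% margin.** The sample size text says 20% but computes with 35%, which is a separate conflict. At 20% the difference is 1.34 × 0.20 = 0.268, and power at 28 per group is about 36%. Adjustment at r = 0.5 raises it only to about 45%.

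What survives is narrower. The text commits the primary comparison to a method that does not use the baseline as a covariate, and it plans baseline tests that serve no purpose in a randomised trial.

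**Conclusion.** The point holds as an improvement and not as the correction of an error. A baseline-adjusted primary comparison would generally be more precise than the planned one and would remove the effect of chance imbalance in the day-0 score.

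The direction rests on the variance algebra and does not depend on r. The size depends on three things that the document does not state: the correlation, what the SD of 0.62 refers to, and the ratio of follow-up to baseline variance. For assumed r from 0.3 to 0.7 with equal variances, the gain is about 6 to 14 points if 0.62 is the SD of change and about 2 to 18 points if it is the SD of a single score. It can be near nil if follow-up variance exceeds baseline variance. No single figure should be quoted as the gain.

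**What to change.** Make the primary result one baseline-adjusted comparison. Either of these would do:

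- ANCOVA of the follow-up primary-outcome score on treatment and day-0 score; or
- a mixed model of the day 15, 30 and 45 scores on treatment, visit, treatment-by-visit and day-0 score, with the treatment contrast at one prespecified visit.

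Day 30, the end of treatment, is a natural choice of visit. Report the adjusted difference with a 95% confidence interval. Because the outcome appears to be graded, add a baseline-adjusted ordinal model as sensitivity analysis. Describe baseline characteristics without significance tests, and do not choose covariates from such tests.

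The model needs the same primary item scored at day 0 and at follow-up. Radiation of pain is named in the sample size text but is not listed by that name under the assessment criteria, so the amendment should identify the item.

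No new visits or patients are needed. The cost is a dated, documented amendment, with the registration updated. Study status says that recruitment has started, so it should be completed before any outcome data are examined.

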### Participant timeline

Patients will be treated for 30 days and assessment will be done up to 45 days as mentioned in
Figure 1.

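### The repeated measures ANOVA option for secondary outcomes would not isolate the day-30 difference; the mixed-model option, with day 0 as covariate, should be chosen

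*Protocol article*

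**What the plan says.** The Statistical methods text of the protocol article (under Data collection plan) reads: "Secondary outcomes will be analyzed using repeated measures ANOVA or mixed-effects models for longitudinal data". Chi-square tests are added for categorical outcomes. The primary outcome is handled apart from this, by t-tests or rank tests of change within and between groups.

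The time schedule under Recruitment says "The intervention period will be from 0 to 30 days and follow up on the 0"th day, continuing with days 15, 30 and 45. Study setting gives the same four visits for all parameters. Table 1 labels the first three visits as during treatment and day 45 as after treatment. Day 0 is therefore the pre-drug baseline, days 15 and 30 are on drug, and day 45 falls 15 days after drug ends.

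One heading does not fit this schedule. The objective criteria (straight leg raising, walking time, Schober's test, bowstring test) are headed as taken before and after only. The Oswestry questionnaire is listed with the subjective criteria, whose heading carries no such restriction.

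**The concern.** Repeated measures ANOVA is the first method named, and these four visits are the only longitudinal data described. With all four as responses, the method gives two between-group tests by default:

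- **Group main effect.** It compares the arms on the mean of the four visits. One is a randomised baseline, where the expected difference is zero. Another is an off-drug visit, where a difference may have faded.
- **Group-by-time interaction.** It has 3 degrees of freedom and shows only that the profiles are not parallel. It does not say at which visit the arms differ, or in which direction.

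Neither test says directly whether the two drugs differ at the end of treatment, or whether a difference persists off drug. At stake is how clearly, and with what power, the trial can answer those questions for secondary outcomes such as the Oswestry score.

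**Working it through.** **The plan's own figure.** The inputs, all from Sample size under Recruitment, are "α=Type I error at 5% at both sides two tailed", z-values 1.96 and 0.84, SD 0.62, and a difference from "1.34 *35) /100 = 0.469". Then n = 2 × (1.96 + 0.84)² × 0.62² / 0.469² = 2 × 7.84 × 0.3844 / 0.21996 = 27.4, rounded up to 28 per group. The stated figure reproduces.

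**Borrowed inputs.** No difference or SD is given for a secondary outcome. The illustration uses those of the sizing variable ("Primary Variable = Radiation of Pain"): 0.469 / 0.62 = 0.76 SD at day 30. It uses 27 per arm, which is 30 less 10%.

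**Assumed inputs.** The within-patient correlation ρ is 0.5 and equal between all visits. The article does not say whether 0.62 is the SD at a visit or of a change. At ρ = 0.5 this makes no difference, because the SD of a change is 0.62 × √(2 × (1 − 0.5)) = 0.62. The effect is zero at day 0 and full at day 30, and it varies at days 15 and 45.

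**Standard errors (n = 27, s = 0.62, ρ = 0.5).**

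- Unadjusted day-30 change: s√(4(1 − ρ)/n) = 0.62 × √(2/27) = 0.169. Ratio 0.469 / 0.169 = 2.78; power 78% (t, 52 df).
- Day 30 with day 0 as covariate: s√(2(1 − ρ²)/n) = 0.62 × √(1.5/27) = 0.146. Ratio 0.469 / 0.146 = 3.21; power 88% (t, 51 df).
- Four-visit main effect: s√(2(1 + 3ρ)/(4n)) = 0.62 × √(5/108) = 0.133. The estimate is 0.469 times the mean of the profile (t, 52 df).
- Interaction: λ = (n/2) × Σ(mᵢ − m̄)² / (s²(1 − ρ)), where mᵢ is the group difference at visit i; F with 3 and 156 df.

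| Share of the day-30 effect on days 0/15/30/45 | Average as share of day 30 | Main effect power | λ | Interaction power |
|---|---|---|---|---|
| 0, ½, 1, ½ | 50% | 41% | 7.7 | 62% |
| 0, ½, 1, 0 | 38% | 25% | 10.6 | 78% |
| 0, ½, 1, 1 | 63% | 58% | 10.6 | 78% |
| 0, 1, 1, 1 | 75% | 73% | 11.6 | 82% |

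The two day-30 contrasts keep 78% and 88% in every row. With 28 per arm they have 79% and 89%, the main effect 26–75% and the interaction 64–83%.

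**Sensitivity to ρ.** The same formulas with ρ from 0.3 to 0.7, over the four profiles and with 0.62 as the SD at a visit, give 21–84% for the main effect, 47–97% for the interaction and 82–97% for the baseline-adjusted day-30 contrast. At ρ = 0.3 with a full, lasting effect, the main effect (84%) slightly exceeds the adjusted day-30 contrast (82%).

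**Where averaging wins.** Take the mean of days 15, 30 and 45, adjusted for day 0, at ρ = 0.5. Its SE is s√((2/n) × ((1 + 2ρ)/3 − ρ²)) = 0.62 × √(2 × 0.4167/27) = 0.109. Its power is 80%, 56%, 94% and 99% in the four rows. It beats day 30 alone when the effect lasts to day 45, and not when it fades.

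**The case against.** The strongest objection is that the article never commits to the weak analysis. It does not say which visits enter the model, whether day 0 is a response or a covariate, or which term decides. A reader might infer that the plan pools all four visits into one omnibus test. That is the default output of one of two permitted methods, not a stated rule. The other method, the mixed-effects model, can give the day-30 contrast from the same data without loss. Model terms and contrasts are also commonly left to an analysis plan, and none is shown here. All of this stands, and it limits the point to a choice between two stated options.

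A reader might also infer that the secondary tests lose power in general. The figures do not support that. Against the unadjusted day-30 change (78%), the interaction is clearly lower in only one of the four profiles. The main effect can match the day-30 contrast when correlation is low and the effect lasts. Part of the gap to 88% is the gain from covariate adjustment, whichever visit is chosen.

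Three further limits stand. The article does not name day 30 as the deciding visit for secondary outcomes, and a comparison of whole profiles is a legitimate question. The effect size belongs to the primary variable, and the profiles and correlations are assumed. If the objective criteria are measured only before and after, the group-by-time test is the same as a t-test of change, and nothing is blurred for them.

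What survives is that the ANOVA option, used with four visits as responses, gives no visit-specific answer and makes poor use of the day-0 value.

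**Conclusion.** The point holds as a conditional one about secondary outcomes. If repeated measures ANOVA is used with days 0, 15, 30 and 45 as responses, neither of its between-group tests isolates the end-of-treatment difference. Its main effect estimates 38–75% of that difference in the profiles examined. At correlation 0.5 and 27 per arm, a baseline-adjusted day-30 contrast has about 10 points more power than an unadjusted day-30 change, 6 to 26 points more than the interaction, and 15 to 63 points more than the four-visit main effect.

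These sizes rest on assumed profiles and correlation and on a borrowed effect size, so they illustrate the point and do not predict results. The point is firmest for the Oswestry score and conditional for the objective criteria. It does not touch the primary analysis or the 28 per group. The gap between the 20% margin in words and the 35% in the calculation is a separate matter.

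**What to change.** For each secondary outcome measured at all four visits, choose the mixed-model option already permitted. Use days 15, 30 and 45 as responses, the day-0 value as covariate, and group, visit and group-by-visit terms. Report the day-30 group difference with its 95% CI as the end-of-treatment effect, and the day-45 difference separately as persistence off drug. Do not rest the conclusion on a group effect averaged over all four visits or on the omnibus interaction. Also reconcile the before-and-after heading of the objective criteria with the four-visit schedule, so that it is clear which outcomes the model covers.

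The cost is one or two sentences on the model and a corrected heading, with no extra visits, data or patients. The trade-off is that day 30 alone has less power than a baseline-adjusted average of the follow-up visits if the effect lasts to day 45. Recruitment has started, so the choice should be recorded before outcome data are examined by group.

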## Discussion

This study will compare the therapeutic efficacy of
*Trayodashang guggul* and
*Rasonapinda* adjuvant to
*katibasti* (oil pooling therapy) in individuals with
*grudhrasi* (sciatica).
*Grudhrasi* has been mentioned in classics in ayurveda under
*vatavyadhi* (neurological disorders caused by Vata, one of the bodily humour) where there is radiating pain along with stiffness in buttocks (sphik) that gradually encroaches posterior aspect of lumbosacral region radiating to the thigh, popliteal area, calf up to the foot sequentially. In ayurveda, treatment means to disintegrates the pathogenesis (samprapti).
^
20
^ In
*grudhrasi* there is mainly vitiation of
*vata* humour along with
*kapha* humour.
^
21
^ Also, there is derangement of digestive strength with vitiation of bones and muscles and ligaments by their improper nourishment which gives rise to the above-mentioned symptoms. The quality of drugs for disintegration of disease pathogenesis should include
*vata* and
*kapha* pacifying action and which also nourishes the body tissues.
^
22
^
*Trayodashang Guggul* is a polyherbal formulation mentioned in ayurveda in which 13 herbs, including
*guggul*, are combined to make
*Trayodashang Guggul*, which is then processed in
*ghrut* (Ghee). Specifically, constituents like
*Asparagus racemosus (shatavari*)
*, Winthania somnifera (Ashvagandha*) and
*Tinospora cordifolia (guduchi*) are known as rejuvenators and provides strength to body tissues.
^
23
^
*Trayodashang guggul* also have proven anti-inflammatory action. Additionally
*Ghrut* (Ghee) with its catalytic and synergistic action helps in better penetration and absorption of drug.
^
24
^ Thus
*trayodashng guggul* directly has an impact in disintegration of disease pathogenesis and pacifying
*vata* humour.
*Rasona Pinda* has been mentioned in
*Bhaisajya Ratnavali* (Ayurveda classics) which consists of
*Rasona* (
*Allium sativum*)
*, Trikatu* (combination of
*zingiber officinale*,
*Piper nigrum* and
*Piper longum*) and
*errand* (
*Ricinus communis*) as chief ingredients possessing a mainly pungent taste (katu, one of the six taste in ayurveda) and hot in potency.
^
25
^
*Allium sativum* is a well-known
*Kapha* and
*Vata* humour pacifying drug.
*Rasona* has rejuvenating action (
*Rasayan*). Being rejuvenating, this medication raise the standard of healthy body tissue production and restored normalcy to the vitiation of bone and tissues.
*Trikatu* (combination of
*zingiber officinale*,
*Piper nigrum* and
*Piper longum*) helps in
*Ama* toxin (undigested food) digestion and enhances digestive fire with its hot potency.
^
26
^
*Trikatu* (combination of
*zingiber officinale*,
*Piper nigrum and Piper longum*) has also been shown to be helpful for musculoskeletal diseases, reducing stiffness and swelling.
^
27
^ Additionally
*Rasona Pinda* tablet given is tritutrated with decoction of roots of
*Ricinus communis* (
*erandmula*).
*Ricinus communis (erandmula)* being sweet
*,* pungent
*,* astringent in taste and unctuous in nature with hot potency will help in combating vitiated
*vata-kapha* bodily humour.
^
28
^
*Kati Basti* (oil pooling therapy) with
*Dashmoola* oil (combination of the roots of 10 herbal drugs) relieves stress from muscles and bones, allowing the
*Srotas* (inner channels of body) to function more efficiently.
^
29
^ It also aids in improved blood circulation and provides flexibility in body movement. Ingredients of
*Dashamula* (combination of the roots of 10 herbal drugs) have
*Vata* and
*Kapha* humour pacifying properties and also possess anti-inflammatory and analgesic action which provides relief from muscular and skeletal discomfort in the back.
^
30
^

